## Methods

### Study Design

Two-arm, parallel, open-label, waiting list, feasibility, pilot randomized controlled trials (RCTs) (Figure 1) will be conducted with older adults, stroke survivors, and colorectal cancer survivors. We will have 1 test case per target population, where different service models (unguided, guided, or blended care) will be tested. The feasibility pilot trials will be performed to identify weaknesses in the study design, test the data collection process, estimate sample sizes, and assess the feasibility of the parent RCTs. The acceptability of Anathema by study participants; the structure, format (ie, unguided, guided, and blended), and content of the study intervention; and between-group differences will also be preliminarily evaluated through this design.

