### Measures

#### Primary Outcome Measures

The primary outcomes in this study are the acceptability, usability, and feasibility of Anathema. To assess Anathema’s acceptability, participants will self-report on the appropriateness and usefulness of the intervention’s content, length, usability, and service delivery model, using a self-developed 5-point Likert scale and the System Usability Scale [51].

Anathema’s feasibility-specific measures include recruitment, randomization, retention, and adherence rates (Table 2). Postintervention semistructured interviews will also be conducted to gather further data on Anathema’s usefulness, usability, and feasibility, as perceived by participants.

**Table 2 table2:** Primary outcome measures.

Outcome	Metrics
Acceptability	Self-developed 5-point Likert scale assessing the appropriateness and usefulness of the intervention’s content, length, usability, and service delivery model Postintervention semistructured interviews
Usability	System Usability Scale [51]
Feasibility	Recruitment: Number of participants screened per week Number of screening failures Number of participants enrolled per week Proportion of recruited participants opting to enroll Randomization: Proportion of eligible participants who access Anathema following randomization ‎Proportion of eligible participants who complete at least one module of Anathema Retention: Proportion of participants who complete T0 (baseline) measures Condition-specific completion rates following randomization (completion is defined as ≥50% of modules accessed at least once) ‎Proportion of participants initiating baseline measures who complete T1 (midtest) and T2 (posttest) measures Adherence: Proportion of participant dropouts from each intervention condition Proportion of participant withdrawals from the study Postintervention semistructured interviews

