#### Enrollment and Randomization

Participants fulfilling all eligibility criteria will be registered and randomized. Simple randomization will be performed by an independent statistician, using a computerized program. Older adults in Austria, and colorectal cancer and stroke survivors in Portugal will be submitted to subsequent simple randomization so that they are randomly assigned to one of the study psychologists. Colorectal and stroke survivors will be guided by study psychologists from SexLab, and older adults in Austria will have access to blended support provided by clinical psychologists from Instahelp. Older adults in the Netherlands will not be submitted to this second randomization procedure, given that they will get access to the self-guided version of the program. Participants randomized to Arm A (experimental condition) will receive immediate access to Anathema. Participants assigned to the WLC condition will gain access to the program approximately 8 weeks after randomization and after being submitted to a second baseline assessment to confirm their eligibility for the study.

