#### Discontinuation of Participation

Participants may withdraw from the study at any time and for any reason, without any consequences, or be dropped from the study by the research team if a severe aggravation of baseline measures occurs. In this case, the participant will be referred to psychology services at study sites or specialized resources in the community. The main reason for withdrawal will be registered, and a final assessment will be performed whenever the participant agrees with it. Participants who are lost to follow-up may be replaced to ensure a balanced number of participants in each study arm.

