### Analysis

Descriptive statistics (ie, means, percentages, frequencies, etc) will be used to characterize the study sample and report on acceptability, usability, and feasibility quantitative measures. Acceptability and feasibility assessments will also be based on the qualitative data collected during the postintervention interviews. Qualitative data will be thematically analyzed [64].

To evaluate Anathema’s preliminary efficacy, we will first perform independent sample *t* tests and chi-square analysis to assess potential baseline differences between participants randomized to the experimental and control arms. Second, we will calculate the differences between the experimental group and the control condition for secondary outcomes. Data analysis will be performed according to the intention-to-treat principle and resorting to a mixed-models approach [65]. Effect sizes (Cohen *d*) [66] and the 95% CI will be calculated to measure the treatment magnitude for continuous outcomes. Finally, clinical significance will be assessed using the Jacobson & Truax method [67]. All statistical analyses will be conducted in IBM SPSS for Windows (IBM Corp).

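### Replacing participants lost to follow-up to keep the arms balanced cannot work under simple randomisation and sits badly with intention-to-treat

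*Protocol article*

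**What the plan says.** The rule stands in the Protocol article under Discontinuation of Participation: "Participants who are lost to follow-up may be replaced to ensure a balanced number of participants in each study arm". The same paragraph also provides that "The main reason for withdrawal will be registered, and a final assessment will be performed whenever the participant agrees with it".

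Four other statements bear on it.

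- Enrollment and Randomization: "Simple randomization will be performed by an independent statistician, using a computerized program". No block or stratum is mentioned, and no separate route for replacements.
- Study Design: "Two-arm, parallel, open-label, waiting list, feasibility, pilot randomized controlled trials (RCTs) (Figure 1) will be conducted".
- Analysis: "Data analysis will be performed according to the intention-to-treat principle and resorting to a mixed-models approach".
- Primary Outcome Measures, Table 2: feasibility is a primary outcome, and its metrics include "Proportion of participants initiating baseline measures who complete T1 (midtest) and T2 (posttest) measures" and "Proportion of participant dropouts from each intervention condition", as well as withdrawals from the study.

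The article does not say how a replacement is allocated. It also does not say whether the person replaced stays in the analysis set and in the Table 2 denominators.

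**The concern.** The sentence gives a purpose, equal arm numbers, that the trial's own allocation method cannot deliver. A site that follows it literally has one way to succeed: put the next eligible person into the arm that has just lost someone. That person's arm is then fixed by an event after randomisation, and staff can know it before enrolment because the trial is open-label. The exclusion criteria leave room for the investigator to judge whether someone can or will comply, so knowing the arm in advance could influence who is admitted.

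The purpose also rests on a completer count. Loss to follow-up does not change how many people were randomised to each arm. It unbalances the arms only if the lost are no longer counted, and intention-to-treat counts them.

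Finally, these pilots exist partly to learn whether parent trials are feasible, and the Discussion concedes that retention is hard to predict. A substitution rule that is silent on denominators leaves that estimate open to misreading.

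**Working it through.** **Inputs.** From the documents: simple randomisation into two arms; open-label; at least 30 participants per target group (Study Population and Research Sites); intention-to-treat with mixed models. The article states no allocation ratio and no dropout rate. I assume 1:1 allocation, a group of exactly 30, and dropout of 10% to 40%. The figure of 30 has no power calculation behind it, so there is no stated result to reproduce.

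**1. Was balance ever a property of this design?** With X ~ Binomial(30, 0.5) in one arm:

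- exact 15:15 split: C(30,15)/2^30 = 14.4%
- 18:12 or more uneven: 2 × P(X ≥ 18) = 36.2%
- 20:10 or more uneven: 2 × P(X ≥ 20) = 9.9%

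The arms are likely to be unequal before anyone is lost.

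**2. Can randomised replacements restore balance?** Each enters the depleted arm with probability 0.5. If k people are lost from one arm, the probability that all k replacements go there is 0.5^k:

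- k = 2: 25%
- k = 4: 6.3%
- k = 6: 1.6%

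Randomised replacements therefore cannot ensure balance. Replacements that do ensure it are not simply randomised.

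**3. Does the analysis need equal arms?** No. A mixed model uses the available data from every randomised participant and does not require equal group sizes. Replacement gives the stated analysis nothing that it needs.

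**4. What could happen to reported retention?** This applies only if replaced participants were removed from the denominator. Let d be the assumed dropout rate. Replacing until 30 complete requires 30/(1 − d) randomised, rounded up. One round of replacement requires 30(1 + d) randomised and gives 30(1 − d)(1 + d) expected completers.

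| Dropout d | True retention | Randomised for 30 completers | Retention read as 30/30 | One round: completers/30 |
|---|---|---|---|---|
| 10% | 90% | 34 | 100% | 29.7/30 = 99% |
| 20% | 80% | 38 | 100% | 28.8/30 = 96% |
| 30% | 70% | 43 | 100% | 27.3/30 = 91% |
| 40% | 60% | 50 | 100% | 25.2/30 = 84% |

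With everyone randomised in the denominator, the one-round case returns the true rate. At d = 20%, for example, 28.8/36 = 80%.

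**5. Do the Table 2 definitions remove the lost?** No. A lost participant who started the baseline measures belongs to the denominator of the T1/T2 completion metric by definition. Dropouts by condition and withdrawals are counted separately. The last two columns above show what a substitution reading would produce, not what Table 2 prescribes.

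**The case against.** The other side has a fair case on several points.

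- **The rule is permissive.** It says that participants may be replaced and names no allocation mechanism. Enrollment and Randomization says that eligible participants are randomised and makes no exception for replacements. This stands to the extent that non-random placement is not explicitly ordered. It does not rescue the sentence, because its declared purpose is unattainable under that procedure.
- **No breach of intention-to-treat is stated.** This also stands. Enrolling extra people while keeping everyone randomised is compatible with the principle, and nothing says that lost participants are deleted. What remains is a conflict of rationale: the stated reason for replacing makes sense only if the lost stop counting.
- **Attrition stays visible.** A reader might infer that the rule conceals dropout. The documents do not support that. Table 2 counts dropouts, withdrawals and all who begin baseline measures, and reasons for withdrawal are recorded.
- **The efficacy contrast.** A reader might also infer that replacement by itself biases the treatment comparison by a calculable amount. It cannot be sized from the documents. If people who are worsening leave one arm more often, the observed means are biased with or without replacement, so that bias cannot be charged to this sentence. The separate risk, selective enrolment when the next arm is known, is real but cannot be quantified here.
- **It is a feasibility pilot.** Efficacy is secondary and preliminary. This limits the consequences but does not make the rule coherent, and the repair is very cheap.

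**Conclusion.** The point holds as a wrongly stated rule, not as a missing detail. The replacement sentence and the randomisation sentence cannot both be followed to their stated ends. Meeting the balance goal means non-random, foreseeable allocation in an open-label trial, and keeping simple randomisation means that the goal is not met. The rationale also conflicts with the intention-to-treat commitment, and the planned model makes equal arms unnecessary.

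The conflict with randomisation does not depend on any dropout assumption; its probabilities assume only 1:1 allocation and, for the split figures, a group of 30. The effect on retention is conditional: 100% in place of 80% to 70% at an assumed 20% to 30% loss, if the lost left the denominators and replacement continued to 30 completers. Under Table 2 as defined, it does not arise. No figure for bias in the secondary outcomes can be attributed to the rule.

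**What to change.** Delete the replacement sentence. If the sponsor wants to be able to top up numbers, replace it with a statement that:

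- any extra participants are newly randomised by the same procedure and reported as additional, not as substitutes;
- every randomised participant stays in the assigned arm and in the intention-to-treat mixed model;
- every randomised participant, including those lost, stays in every applicable Table 2 denominator.

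The article reports 49 participants randomised by May 2023 with recruitment continuing. Any replacement already made should therefore be identified and its method of allocation reported.

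The cost is a short amendment. Final arm sizes may be slightly unequal, which the analysis tolerates. Reported retention may be lower than under a count that left out the lost, but it will be the figure that the parent trials need.

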#### Data Handling and Storage

All data to be collected within the scope of Anathema will be completed by participants via the Anathema app and through regular outcome assessments. Questionnaire data will be collected through LimeSurvey [62] and Microsoft Office Forms. These surveys will exclude personal information and IP storage, so that confidentiality and anonymity are ensured. Each participant will be assigned a random user, and this will be used by researchers to identify the participants and their survey responses during the study. Feasibility and trial-related data will be monitored via TrialMonitor [63], a software tool that scaffolds the creation of personalized web dashboards for monitoring participants in technology-enabled field trials. Data will be kept confidential and will be stored in compliance with physical infrastructure and software requirements imposed by the European Union (EU), namely the EU Regulation 2016/679 of The European Parliament and of the Council of April 27, 2016, on the protection of natural persons with regard to the processing of personal data and on the free movement of such data. The questionnaire responses and data from the application will be stored in a secure database that is not accessible from the outside world without proper authorization. The data will be protected by multiple layers of security to ensure that it remains confidential and can only be accessed by authorized personnel. The database will be regularly backed up to ensure that the data are not lost in case of any unforeseen events. Additionally, strict protocols will be in place to track and monitor any access to the data, to ensure that the data are only being used for authorized purposes. All communication related to Anathema will take place within the developed platform, so no confidential information is sent unencrypted and via third-party programs.

Regarding physical infrastructure, data will be stored in servers that are physically located on the premises of Associação Fraunhofer Portugal Research in Porto, Portugal. These servers are situated in a locked server room that is equipped with a key and card-keypad access control system, and is accessible to only authorized personnel. A dedicated division of IT technicians, working at Associação Fraunhofer Portugal Research, is responsible for the maintenance of the hardware equipment (servers and network), ensuring that all equipment is constantly running and is redundant (various hardware backups ensure continuity if one system fails). The software on the servers is updated constantly. Additionally, full backups of the system are performed on a daily basis and stored at a different location than the live servers. These backups are encrypted. The server operating system is Linux-based, and the operating system installation is dedicated only to the platform services. Encrypted (https/Transport Layer Security) protocols will be used in all data communication between the servers and the users, as well as in peer-to-peer audio/video chat. The key to produce the code that allows the indirect identification of the participants will be deleted 5 years after the end of the study, as mandated by Deliberação n. 1704/2015 (Deliberação da Comissão Nacional de Proteção de Dados Aplicável aos tratamentos de dados pessoais efectuados no âmbito de Investigação Clínica).

Instahelp uses 3 different security mechanisms to protect data from external access: (1) encryption of data before transmission (end-to-end encryption), (2) secure data transmission (Transport Layer Security), and (3) 2-factor authentication. The widely used and recognized LibSodium cryptography library is used to encrypt the data. Each individual chat message is encrypted with a symmetric space key based on the Salsa20 (64-bit) method. In addition, each message is checked for tampering after transmission using message authentication via Poly 1305MAC. The hosting of the web server (including the implementation on the server side) and the database are provided by the IT service provider 1&1 in Frankfurt (Germany).

### Analysis

Descriptive statistics (ie, means, percentages, frequencies, etc) will be used to characterize the study sample and report on acceptability, usability, and feasibility quantitative measures. Acceptability and feasibility assessments will also be based on the qualitative data collected during the postintervention interviews. Qualitative data will be thematically analyzed [64].

To evaluate Anathema’s preliminary efficacy, we will first perform independent sample *t* tests and chi-square analysis to assess potential baseline differences between participants randomized to the experimental and control arms. Second, we will calculate the differences between the experimental group and the control condition for secondary outcomes. Data analysis will be performed according to the intention-to-treat principle and resorting to a mixed-models approach [65]. Effect sizes (Cohen *d*) [66] and the 95% CI will be calculated to measure the treatment magnitude for continuous outcomes. Finally, clinical significance will be assessed using the Jacobson & Truax method [67]. All statistical analyses will be conducted in IBM SPSS for Windows (IBM Corp).

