### Study Population and Research Sites

This research will target 3 study populations: older adults, colorectal cancer survivors, and stroke survivors. Older adults will be recruited in the Netherlands and Austria. Colorectal cancer survivors and stroke survivors will be recruited in Portugal. A minimum of 30 participants [38,39] per target group is expected to participate in the study trials.

The criteria presented in Textbox 1 will be used to check eligibility for participation in the study:

The study will be conducted at 5 different research sites: Unie KBO in the Netherlands; Instahelp in Austria; and IPO-Porto, Europacolon Portugal, and Centro de Reabilitação Profissional de Gaia in Portugal. Sites invited to participate were selected owing to their working standards and resources.

Eligibility criteria for Anathema’s feasibility randomized controlled trials.

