#### Study Intervention Delivery and Assessment

After randomization, participants will gain access to Anathema either via the co-developed app (older adults in the Netherlands, and colorectal cancer and stroke survivors in Portugal) or the Instahelp platform (older adults in Austria). At this stage, the 3 abovementioned service models will be tested for acceptability, feasibility, and preliminary efficacy.

The self-guided model will be tested with older adults in the Netherlands. Participants will gain access to the treatment modules every week, being prompted to complete the modules in approximately 1 week. If participants fail to complete the modules in the specified time frame, a reminder will be sent. Upon completion, participants will receive access to the following module. The preliminary efficacy of the intervention will be assessed at midtest (T2) and after the completion of the program at posttest (T3), using the measures listed above.

The guided model will be trialed by colorectal cancer and stroke survivors in Portugal. Participants will gain access to the intervention after a preliminary online or telephone appointment is conducted with their assigned study psychologist. This first e-appointment aims to discuss the program’s structure, report the baseline findings, and tailor the intervention according to participants’ needs and preferences. Once clinical psychologists and participants reach an agreement, the selected modules will be prescribed and made available weekly to the participants. Participants will be prompted to complete the modules in approximately 1 week. Within 24 hours of module completion, the study psychologists, based on the reported outcomes, will assess participants’ progress and determine whether it is appropriate or not for the participants to proceed to the next module. If so, participants will receive access to the following module. If not, study psychologists will instruct participants on what needs to be completed to advance to the next module. The preliminary efficacy of the intervention will be assessed at midtest (T2) and after the completion of the program at posttest (T3), using the measures listed above.

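### Cohen d is the planned effect size in pilots of about 15 per arm; reporting Hedges g instead would remove an expected overstatement of about 3% at no cost

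*Protocol article*

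**What the plan says.** The Analysis section names the measure of treatment magnitude: "Effect sizes (Cohen *d*) [66] and the 95% CI will be calculated to measure the treatment magnitude for continuous outcomes". It gives no formula, standardiser or small-sample correction. The sentence follows one that plans an intention-to-treat analysis with mixed models.

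The size of the pilots is given under Study Population and Research Sites: "A minimum of 30 participants [38,39] per target group is expected to participate in the study trials". Study Design describes two-arm trials with one test case per target population. Enrollment and Randomization says "Simple randomization will be performed by an independent statistician, using a computerized program" and gives no allocation ratio.

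Two further statements bear on how the effect sizes might be used. Study Design lists among the aims to "estimate sample sizes, and assess the feasibility of the parent RCTs". Study Intervention Delivery and Assessment says that "the 3 abovementioned service models will be tested for acceptability, feasibility, and preliminary efficacy". Two of those models, self-guided in the Netherlands and blended in Austria, fall within the single older-adult population.

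**The concern.** Cohen d divides a mean difference by an estimated SD. In small samples the expected value of that ratio is larger in absolute size than the true standardised difference. This is a bias in the point estimate. It is separate from the width of the interval, and reporting a 95% CI does not remove it. The corrected version, Hedges g, is d multiplied by a factor that depends on the degrees of freedom.

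The choice matters a little more here than in most reports because the pilots are partly meant to inform the size of later trials. Required sample size varies with 1/d², so a small relative bias in d roughly doubles in the sample size, and it acts toward a parent trial that is too small.

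**Working it through.** The article gives no effect size, SD, alpha or power, and its minimum of 30 rests on citations. There is therefore no calculation of the plan's own to reproduce. The check below gives only the size of the bias.

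**Inputs**
- At least 30 per target group, two arms (from the article).
- Assumed: exactly 30, allocated 1:1, so 15 per arm and df = 28.
- Assumed: a two-sample d standardised by the pooled SD.
- Assumed for the parent trial: two-sided alpha 0.05, 80% power, true d 0.5.
- Further assumption, for an outer case only: older adults split evenly between the two countries, with a separate d for each, so 7 + 8 per country and df = 13.

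**Correction factor.** J(df) = Γ(df/2) / [√(df/2) · Γ((df−1)/2)], and E[d] = δ/J.
- df 28: J = 0.9729 (the usual approximation 1 − 3/(4·28 − 1) gives 0.9730). Overstatement 1/J − 1 = 2.8%.
- df 13: J = 0.9410. Overstatement 6.3%.
- For comparison, all 90 participants pooled at 45 per arm (df 88): J = 0.9914. Overstatement 0.9%.

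A simulation of 300,000 pilots at true d 0.5 agreed closely, with a mean d of 0.515 at 15 + 15 and 0.534 at 7 + 8.

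**Effect on a parent trial sized from the expected uncorrected d.** The sample size is multiplied by J², and the power is Φ((1.960 + 0.842)·J − 1.960).
- df 28: J² = 0.947, so 5.3% too small. Power = Φ(2.802 × 0.9729 − 1.960) = Φ(0.766) = 77.8%. By the normal formula n = 2(1.960 + 0.842)²/d², this is 60 per arm instead of 63.
- df 13: J² = 0.885, so 11.5% too small. Power 75.1%, and 56 per arm instead of 63.

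**Bias against sampling error at true d 0.5.** SE = √[(n₁ + n₂)/(n₁n₂) + d²/(2(n₁ + n₂))].
- 15 + 15: SE = √(30/225 + 0.25/60) = 0.371. Bias = 0.5 × 0.028 = 0.014, about 4% of one SE. Approximate 95% CI −0.23 to 1.23.
- 7 + 8: SE = √(15/56 + 0.25/30) = 0.526. Bias 0.031, about 6% of one SE. Approximate 95% CI −0.53 to 1.53.

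**How often the estimate is too high.** In the simulation, d exceeded the true value in 50.7% of pilots (15 + 15) and 50.9% (7 + 8). The corrected estimate did so in 49.1% and 48.6%.

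**The case against.** The strongest reply is that the article nowhere says the d is uncorrected. Cohen d is sometimes a loose label for any standardised mean difference, and the exact formula is the kind of detail that an article leaves to an analysis plan. This stands as a caution: a correction may be intended. It does not remove the point, because the article does name a measure. As normally defined, that measure carries no correction, and the corrected one has its own name.

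The reply is also right that the percentages are not fixed by the document. The factor J above belongs to a pooled-SD two-sample d. If d is derived from the mixed model, the standardiser and degrees of freedom may differ. Any recruitment above 30 shrinks the bias.

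Three stronger readings are tempting and are not supported:
- *That the parent trials will be too small.* The article does not say that the observed d will size them; the input could equally be an SD, a retention rate or a difference judged worthwhile. Even if d were used, the bias is in expectation and not in every estimate. The simulation shows that the correction hardly changes how often a single pilot overestimates the effect.
- *That the 11.5% shortfall and 75% power are the likely result.* These need an even country split and a separate d for each country. The article says that each service model will be tested for preliminary efficacy, but the Analysis section plans no per-country effect size. The Discussion speaks of parent trials in the three target populations.
- *That the Dutch and Austrian groups would look better than the Portuguese groups.* At true d 0.5 the extra bias is 0.031 − 0.014 = 0.017, against a standard error of √(0.371² + 0.526²) = 0.64 for the difference. No ranking of the models is planned.

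**Conclusion.** The point holds as a small, cost-free improvement. At the minimum size, with 1:1 allocation and a pooled-SD d, the named measure overstates the effect by about 2.8% on average. Used to size a parent trial, that means about 5% too few participants and about 2 points of power lost at an assumed true d of 0.5. The figure of about 6% applies only under the added assumption of separate Dutch and Austrian effect sizes.

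Sampling error is by far the larger hazard in sizing a trial from pilots like these. The correction does not cure it; the planned 95% CI at least shows it. Nothing in the article is contradictory on this point, and no conclusion of the trial would turn on it.

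**What to change.** In the Analysis section, replace Cohen d with Hedges g (d multiplied by the small-sample correction) and its 95% CI for all continuous outcomes. If an observed effect size enters any parent-trial calculation, use g together with its CI.

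The cost is one changed formula. It needs no new data and no change of design. At 15 per arm the reported effects become about 3% less favourable (1 − 0.973 = 2.7%).
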